##### Primary clinical outcome to signal efficacy and inform a definitive power calculation

Change in percentage acid contact time pH <4 with the device in situ measured using nocturnal data from 24-hour pH monitoring at initial gastroenterology screening visit and follow-up gastroenterology assessment post-therapy.

#### Secondary outcome measures

Patient acceptability of the trial measured using qualitative interviews throughout the trial.Hours that device is worn during sleep measured using the average number of hours worn per night as detected from the output from the therapeutic device throughout the trial period.To assess the most sensitive quality of life questionnaire prior to the full trial by recording EuroQol 5-dimension 5-level (EQ-5D-5L),^22^ ICEpop CAPability measure for the adult population (ICECAP-A)^23 24^ and the Short Warwick-Edinburgh Mental Wellbeing Scale (SWEMWBS^25^) at baseline and post-intervention.Rating of both therapies measured using a Visual Analog Scale at day 2 of final assessment visit (trial completion).Number of potential participants identified by the care team with and without screening of referral letters measured using number of participants identified on clinics before the prescreening clinic and after the pre-screening.Change in Reflux Symptom Index (RSI)^26^ using changes detected in the RSI validated questionnaire at baseline and post intervention.Change in Epworth Sleepiness Scale (ESS)^27^ using changes detected in the ESS validated questionnaire at baseline and post intervention.Change in cough using changes detected in the validated Leicester Cough Questionnaire^28^ at baseline and post intervention.To identify and measure indicative costs and outcomes and select suitable economic outcomes measured by documenting health resource use including intervention costs, appointment times and attending healthcare practitioners throughout the trial.To determine the acceptability of the intervention and economic data collection methods measured using qualitative questions at the qualitative interview (various timepoints).

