## Methods and analysis

### Study design

This will be a single-centre, single-blinded, tertiary care-based, interdisciplinary parallel 1:1 randomised controlled study. The trial has been registered on ISRCTN (https://doi.org/10.1186/ISRCTN16013232).

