#### Outcomes

##### Primary outcome measures

Percentage of approached patients who were screened for the trial measured using the percentage of patients eligible of those screened at ay 2 of the screening visit.Percentage of eligible patients who were randomised measured using the percentage of screened patients who met the eligibility criteria versus those who were randomised at the randomisation timepoint.Percentage of patients who completed the trial measured using number of patients who were randomised versus those who completed the trial at Day 2 of the final visit.

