### Titration of devices and repeat assessment

The CPAP mask will be delivered as standard of care and, therefore, may be different for each patient. The same CPAP therapy allocated to the participant will be used in the follow-up investigation. Some adjustment of the devices may be needed to ensure comfort and efficacy of the device. This will be done as routine care and scheduled as needed.

Following successful titration for each device and a 3-week customisation period, the 24-hour impedance monitoring and home sleep study will be repeated. As at visit 1, participants will be asked to cease their PPIs, H2-receptor antagonists or antacids. A dental examination will be carried out by the research dentist to ensure there have been no changes in the oral cavity. Participants will be asked to review their diet diary from the day they first did the test and repeat what they ate or drank as closely as possible for the day. That afternoon the participant will attend the oesophageal physiology laboratory. Participants will repeat the RSI questionnaire, ESS questionnaire, Leicester Cough Questionnaire and a QoL questionnaire. The pH impedance testing and Watch-PAT testing will be repeated as described above. Compliance levels for the MAD and CPAP therapy on the same night will be obtained.

On returning the next day to have their pH probe removed and to return the Watch-PAT, participants will be asked to complete a questionnaire about their views in taking part in the study.

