### Sample size

There are several studies investigating change in per cent acid exposure from baseline while wearing the CPAP device. Sample sizes suggested from current data based on change in total acid were between 86 to 168 per group (excluding any attrition).^12 39^ Using the smallest effect size published (Tawk *et al*^12^), assuming a one-sided non-inferiority design with a margin of 4.15 (per cent total acid) together with an SD of 10.8 with a power of 90% and alpha of 2.5% for a definitive study, this would require a sample of 288 (without attrition). Considering the likelihood of the main study finding an effect of this size within a 80% CI, then an approach taken by Cocks and Torgerson^40^ requires a feasibility sample equivalent to approximately 9% of the proposed definitive sample requiring 26 participants. Accommodating an overall attrition rate, including tolerance to the devices, of 40% requires a sample of 44 to be randomised. A sample of 44 will also give us a 95% CI of +/−14% around the attrition rate.

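### The therapy VAS is scheduled only at trial completion, so up to about 18 of 44 ratings may be missing and those collected would largely come from patients who tolerated their device

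*Protocol article*

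**What the plan says.** The list under *Secondary outcome measures* gives the rating one time point: "Rating of both therapies measured using a Visual Analog Scale at day 2 of final assessment visit (trial completion". No rating at discontinuation is described.

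Under *Primary outcome measures*, completion is assessed from the "number of patients who were randomised versus those who completed the trial at Day 2 of the final visit". The rating and the definition of a completer therefore share one event.

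*Titration of devices and repeat assessment* places the repeat monitoring after successful titration and a three-week customisation period. The Abstract says that monitoring is done with the device worn.

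*Sample size* states: "Accommodating an overall attrition rate, including tolerance to the devices, of 40% requires a sample of 44 to be randomised".

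*Study design* describes an "interdisciplinary parallel 1:1 randomised controlled study", and the eligibility criteria exclude previous users of either therapy, so each participant's experience is of one device.

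*Statistical analysis* plans between-arm mean differences with 95% CIs by intention to treat, with a per-protocol analysis considered as sensitivity. *Qualitative interviews* plans about 16 interviews across several groups, one of which is patients who could not tolerate the device.

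**The concern.** A rating of a therapy should carry the opinion of people who disliked it enough to stop. Here the only scheduled rating comes after the point by which many of them may have left. What is collected is then closer to satisfaction among those who tolerated the device than to a rating among those who were given one. Analysis by intention to treat does not repair this, because a participant who does not reach the visit has no scheduled VAS value.

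Two distortions are possible. If those who stop would rate lower, each arm's mean is too high. If, in addition, one arm loses more patients than the other, its mean is inflated more and the comparison is biased towards it. The change in acid contact time has to be measured with the device in place, so losing patients who stopped is hard to avoid there. A rating has no such constraint.

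The wording also needs care. A rating of both therapies cannot come from any single participant's experience in this parallel design.

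**Working it through.** **1. The plan's own figures.** *Sample size* uses "a margin of 4.15 (per cent total acid) together with an SD of 10.8 with a power of 90% and alpha of 2.5" (per cent), and says "this would require a sample of 288 (without attrition". The usual non-inferiority formula with no true difference gives, per arm, 2 × 10.8² × (1.960 + 1.282)² / 4.15² ≈ 142.3. Rounded up that is 143 per arm, or 286 in total, close to 288. The feasibility sample is "approximately 9% of the proposed definitive sample requiring 26 participants": 0.09 × 288 = 25.9, rounded up to 26. Allowing for 40% attrition, 26 / (1 − 0.40) = 43.3, rounded up to 44. The plan's 44 is reproduced.

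**2. Ratings at risk.** At the planned rate, 44 × 0.60 = 26.4 participants reach the final visit and 44 × 0.40 = 17.6 do not. So about 26 ratings are expected and up to about 18 may be missing.

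**3. Size of the distortion.** The protocol gives no arm-specific dropout, VAS mean or VAS SD, so everything in this step is an assumption. Let arms A and B have dropout d_A and d_B. Let completers rate 70 on a 100-point scale, and those who stop rate m, with the same values in both arms.

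- True arm mean = (1 − d) × 70 + d × m.
- Completers' mean = 70, so inflation in an arm = d × (70 − m).
- Bias in the between-arm difference = (d_A − d_B) × (70 − m), towards the arm with the larger d.

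| Dropout A v B (40% overall) | m | True means A, B | Completers' means | Bias towards A |
|---|---|---|---|---|
| 40% v 40% | 30 | 54, 54 | 70, 70 | 0 |
| 40% v 40% | 50 | 62, 62 | 70, 70 | 0 |
| 50% v 30% | 30 | 50, 58 | 70, 70 | 8 |
| 50% v 30% | 50 | 60, 64 | 70, 70 | 4 |
| 60% v 20% | 30 | 46, 62 | 70, 70 | 16 |
| 60% v 20% | 50 | 58, 66 | 70, 70 | 8 |

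**4. A second model.** Suppose latent ratings are normal with equal true means in the two arms, and have correlation ρ with staying on the device. Inflation among completers, in SD units, is ρ × φ(c) / (1 − d), where φ is the standard normal density and c its d-quantile. The factor φ(c) / (1 − d) is 0.798 at d = 50%, 0.497 at 30%, 0.966 at 60% and 0.350 at 20%. With ρ from 0.3 to 0.7:

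- 50% v 30%: ρ × (0.798 − 0.497) = 0.09 to 0.21 SD towards the arm that loses more.
- 60% v 20%: ρ × (0.966 − 0.350) = 0.18 to 0.43 SD.
- 40% v 40%: 0, although both arms are inflated by ρ × 0.644 = 0.19 to 0.45 SD.
- ρ = 0: no inflation and no bias at any dropout.

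Both models agree. Inflation needs lower ratings among those who stop. With a common rating gap, between-arm bias also needs unequal dropout.

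**The case against.** Several stronger readings are tempting, and the case against them is sound.

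- *Those who stop never rate the device.* A reader might infer this, but the article does not say it. Only the repeat monitoring is tied to successful titration. Nobody who stops is said to be withdrawn or barred from the final contact, and *Statistical analysis* lists adherence and follow-up rates as separate summaries. What stands is that no rating is scheduled for anyone who does not reach that visit.
- *The ratings will favour the less tolerated therapy.* That needs unequal dropout and lower ratings among those who stop, and the protocol supplies neither. Even in the illustrations the completers' means are equal: a true difference is hidden, not reversed. The Introduction's remark on better compliance with MADs is about the proportion of the night for which reflux is suppressed, so it does not show that more patients would give up CPAP.
- *18 ratings will be lost.* The 40% is a planning allowance covering other losses as well as intolerance. Some participants may be lost before receiving a device or lost to all contact, and no schedule would recover their ratings.
- *The VAS is missing from the day-2 procedures.* The titration section mentions only that "participants will be asked to complete a questionnaire about their views in taking part in the study". But the schedule of events is in a supplemental table that is not shown, and the legend of Figure 1, also not shown, defines VAS. This is no finding.
- *The outcome asks each participant to rate two therapies.* The phrase can mean that the scale is used in both arms. It is loose wording, not a design error.

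Tolerance is also captured by completion, hours of wear, adherence summaries and interviews. These put completers' ratings in context, but none of them gives a VAS score for those who stopped.

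**Conclusion.** The point holds in a limited form. The single time point coincides with trial completion, so following the plan as written yields ratings mainly from people who tolerated their device, with up to about 18 of 44 missing at the planned attrition.

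Inflation of both arms' means is conditional on lower ratings among those who stop. A between-arm bias further requires intolerance to differ by arm; it is nil if dropout is equal and the rating gap is the same in both arms. Under the assumed inputs above it ranges from 0 to 16 points on a 100-point scale, or 0 to 0.43 SD. These are illustrations, not estimates, and the true size cannot be derived from the document.

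The outcome is secondary, in a feasibility study with no hypothesis testing. The sample size of 44 and the primary feasibility conclusions are unaffected. The change is optional, but worth making because it is cheap.

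**What to change.** In *Secondary outcome measures*, reword the outcome to *rating of the allocated therapy (VAS)*. Collect it from every randomised participant who received a device: at day 2 of the final visit, or, for those who do not reach it, at the contact when the device or the trial is stopped, by telephone if needed. Report ratings by arm for all users first, then for completers, beside arm-specific completion.

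The cost is one VAS item at a discontinuation contact plus the wording. Expected ratings would rise from about 26 to at most 44; the actual gain depends on how many non-completers received a device and can be contacted. The downside is that ratings would then be given after different lengths of use, which reporting completers separately makes visible.

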### Participants and recruitment

Potential participants will be identified by the direct care team either by running a search text function to screen their referral letters or by their consultation in clinic. Patients referred for investigation of OSA, who also have a previously confirmed diagnosis of GORD with a 24-hour pH study or typical heartburn and/or regurgitation >3 times per week and Reflux Disease Questionnaire questionnaire score of >50%, will be informed by their direct care team that they may be eligible to be included in the study and asked if they would like to speak to a research dentist or nurse about participation. The prescreening questions for dental examination will ask patients if they have at least 10 teeth in each jaw, no loose teeth, fillings or caps or obvious holes in your teeth. Interested participants, who meet the pre-screening criteria, will be provided with a patient information sheet of the entire trial and invited to have a dental screening during their gastroenterology appointment, followed by a combined home sleep study and 24-hour pH impedance oesophageal monitoring. It will be explained that participation in the trial will be dependent on meeting the strict inclusion criteria, but they will be reimbursed for the screening appointment.

### Inclusion/exclusion criteria

Patients will be included in the study if they are:

Aged 18 or over.Confirmed OSA with Apnoea-Hypopnoea Index score between 10 and 50,Confirmed GORD with greater than 6% of acid exposure time <pH 4 over 24 hours.No previous CPAP or MAD therapy.Sufficient healthy teeth to support an MAD, that is, 10 teeth in each jaw, no periodontal pockets >5, no frank cavitation or loose crowns/bridges.Willing and able to provide informed consent to the study.

Patients will be ineligible if:

Pregnant or breast feeding.Unable or unwilling to stop GORD medication 2 days prior to assessment or unable to undergo manometry and pH impedance testing.Known liver disease or oesophageal/gastric varices.Previous surgery or intervention for reflux such as fundoplication, which may preclude pH impedance testing.Any previous treatment for oesophageal neoplasia.Unable/unwilling to tolerate either a CPAP mask or an MAD,Medical history likely to impact on 24-hour impedance testing, for example, bulimia nervosa,Participation in other research within previous 30 days.

### Study screening procedures

Following written informed consent by a trained member of the research team, participants will undergo assessments at a screening visit to ensure eligibility is met. Participants will be informed that PPIs will need to be stopped 7 days prior and H2-receptor antagonists or antacids 48 hours prior to this visit. Participants will complete an RSI questionnaire, ESS questionnaire, Leicester Cough Questionnaire and several QoL questionnaires. A full dental examination will be conducted to ensure that participants are dentally fit to wear an MAD if allocated to this intervention. For the gastroenterology assessment, the patient will initially need to undergo high-resolution manometry (HRM). Following local analgesia of the nares the catheter will be introduced transnasally and the patient instructed to drink water through a straw while the HRM catheter is advanced to the stomach. The HRM catheter depth will be adjusted to ensure manometric visual of the upper oesophageal sphincter, the gastro-oesophageal junction and gastric pressures. Ten single swallows of 5 mL will be performed with each being 20 s apart. Each 5 mL water swallow will be assessed in accordance with Chicago classification (V.3) using Manoview software (V.3) (Sierra Scientific Instruments). The HRM catheter will then be removed.

Patients will then undergo reflux monitoring using Sandhill Scientific multichannel impedance pH catheters (ZANBG-44), which are inserted transnasally after applying local anaesthesia (xylocaine). The dual pH sensors of the catheter will be positioned 5 cm below and above the manometric LOS. The impedance sensors will be positioned above the LOS by 3 cm, 5 cm, 9 cm, 15 cm and 19 cm. The data will be captured by ZepHrTM recording device.

For the 24 hours while the probe is inserted, the participant will be asked to complete a food diary as food and drink will impact on their reflux. Stopping reflux medication and the food diary are part of standard care for this procedure.

Following placement of the catheter, participants will be invited for their home sleep study. A type 3 sleep study device, the WatchPAT 200 (WP200; Itamar Medical, Caesarea, Israel) will be given in addition to comprehensive instructions on how to perform a home sleep study. A 24-hour number for technical support will be provided to the patient. After their overnight sleep study, they will return the following day to the gastroenterology department for removal of the probe and return of the WatchPAT.

The gastroenterology data will be captured by ZepHrTM recording device and data will be analysed using the BioVIEW Analysis software (V.5.7.1.0). The sleep study data will be analysed by a qualified sleep technician.

### Randomisation procedures

Participants who meet the inclusion/exclusion criteria will be allocated 1:1 using fixed-block randomisation by the purpose-built computer-generated randomisation service provided by King’s Clinical Trials Unit (KCTU) to either the CPAP (n=22) or the MAD (n=22) arm. Once the participant identifier is entered into the system, an e-mail will be sent to the principal investigators and trial manager informing them of the allocation.

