**Methods:**

This will be a single-centre, single-blinded, tertiary-care based, interdisciplinary, parallel randomised controlled study. Potential OSA participants presenting to the sleep department will be pre-screened for GORD using validated questionnaires, consented and invited to receive simultaneous home sleep and oesophageal pH monitoring. Those with confirmed OSA and GORD (n=44) will be randomly allocated to receive either CPAP (n=22) or MAD therapy (n=22). Following successful titration and 3 weeks customisation period, participants will repeat the simultaneous sleep and oesophageal pH monitoring while wearing the device. The number of patients screened for recruitment, drop-out rates, patient feedback of the study protocol, costs of interventions and clinical information to inform a definitive study design will be investigated.

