### Blinding

This is a single-blinded study. The statistician is the only member of the team who can be blinded to the allocation. The database has been created such that the intervention is not known to the statistician when performing the analysis. The patient and clinician cannot be blinded to the group allocation due to the nature of the therapeutic devices used. However, the objective, computer-generated clinical measurement outcome in for the definitive trial is less likely to be subject to bias.

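### A constant block size in an open, single-centre trial makes some allocations foreseeable; randomly varying block sizes, withheld from the site, would remove most of that certainty

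*Protocol article*

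**What the plan says.** Under Randomisation procedures the protocol article fixes the method: "Participants who meet the inclusion/exclusion criteria will be allocated 1:1 using fixed-block randomisation by the purpose-built computer-generated randomisation service". Once a participant identifier has been entered, "an e-mail will be sent to the principal investigators and trial manager informing them of the allocation". No block length, stratification factor or variation in block size is given.

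Study design describes one centre: "This will be a single-centre, single-blinded, tertiary care-based, interdisciplinary parallel 1:1 randomised controlled study". Under Blinding, "The statistician is the only member of the team who can be blinded to the allocation", and "The patient and clinician cannot be blinded to the group allocation due to the nature of the therapeutic devices used". The word single-blinded therefore refers to the analyst; for those who enrol and treat, the trial is open.

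The abstract gives the number to be allocated as 44, with 22 per arm. Most inclusion criteria are measured: AHI between 10 and 50, acid exposure above 6%, and listed dental requirements. One exclusion is a matter of judgement: "Unable/unwilling to tolerate either a CPAP mask or an MAD". Study screening procedures places written consent before the screening assessments, and so before randomisation.

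**The concern.** With 1:1 blocks of constant length, the last allocation in every block is determined by those before it, and sometimes earlier ones are too. A central service hides the list but not this regularity. Here all allocations form one sequence at one site, and the people who receive the e-mails see all of it. Once the block length is guessed or worked out, they can tell when the next arm is settled.

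By then the patient's AHI and acid exposure are known, because both are eligibility criteria. Foreknowledge could affect whether a patient is judged able to tolerate either device, or when the identifier is entered. Two results are exposed:

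- the percentage of eligible patients randomised, which is a primary feasibility outcome;
- the composition of the arms in the acid-contact-time comparison. This is planned as an unadjusted mean difference and is meant to inform the definitive trial's power calculation.

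The Blinding section relies on the clinical outcome being objective. That protects the measurement; it does not affect who enters which arm.

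**Working it through.** **Inputs.** 44 patients, 1:1, one sequence (abstract, Study design, Randomisation procedures). The article gives no block length and no predictability figure, so there is no stated value to reproduce. Lengths of 2, 4, 6 and 8 are assumptions that show the range.

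**Step 1: certain allocations per complete block.** In a block of length 2m, an allocation is certain once either arm has had its m places. The expected number is 2m/(m+1) per block, a share of 1/(m+1). Check for length 4: the fourth allocation is always certain (1), and the third is certain if the first two agree (probability 1/3), giving 1 + 1/3 = 4/3. The formula gives 4/3 as well.

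**Step 2: 44 patients, length known from the start.** Lengths 6 and 8 do not divide 44, and their incomplete last blocks (2 and 4 patients) are too short to contain a certain allocation.

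| Block length | Complete blocks × certain per block | Certain of 44 | Best guess correct |
|---|---|---|---|
| 2 | 22 × 1 | 22.0 (50%) | 75% |
| 4 | 11 × 4/3 | 14.7 (33%) | 71% |
| 6 | 7 × 1.5 | 10.5 (24%) | 68% |
| 8 | 5 × 1.6 | 8.0 (18%) | 66% |

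The best guess names the arm that is behind in the current block and tosses a coin when the arms are level. For length 4 it is right with probability 1/2, 2/3, 2/3 and 1 at the four positions: 2.833/4 = 71%. Simple randomisation would give 0% certain and 50% guessed correctly.

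**Step 3: length not known but inferred.** A list made of blocks of 4 is also a valid list of blocks of 8, so the results alone never rule out the larger length. I simulated an ideal observer who starts with equal belief in lengths 2, 4, 6, 8 and 10 (an assumption). The median number of allocations before the true length reached 95% probability was 32, 36, 32 and 20 for true lengths 2, 4, 6 and 8. The allocations this observer could call with at least 95% probability averaged about 13, 7, 5.5 and 5 of 44. A team that simply guesses the right length at the outset is back at the table in step 2.

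**Step 4: randomly varying lengths.** Simulation of 44 patients, with a guesser who knows which lengths are in the mix but not their order:

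| Lengths | Certain of 44 | Best guess correct |
|---|---|---|
| fixed 4 | 14.7 | 71% |
| 4 and 6, equally likely | about 2.5 | 69% |
| 4, 6 and 8, equally likely | about 1 | 68% |

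Varying the lengths removes most of the certainty but only a little of the advantage in guessing.

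**The case against.** The strongest reply is that the opportunity is narrow and the stakes are low.

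- **Eligibility is largely measured.** AHI and acid exposure are instrument readings with fixed limits. Dental fitness has explicit criteria and is examined before the overnight data exist. Consent comes first. This stands and shrinks the scope, but the tolerance or willingness criterion and the moment of entry remain discretionary.
- **The counts assume knowledge that the team may not have.** This stands too. They are upper bounds, and step 3 gives lower figures for a team that has to learn the length.
- **The e-mail is unavoidable.** Someone must know the arm in order to deliver the device, and the article does not say that the people e-mailed are the ones who enrol. The notification is not the fault; the constant block length is.
- **The study tests no hypotheses.** Correct, and it lowers the severity. The estimate and the randomised share are still meant to feed the definitive trial.
- **Withholding the block length may be covered in the full protocol.** Possibly, and silence on it is no finding. But the article does fix the constant length, and secrecy does not prevent a guess or inference.

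A reader might infer that the team can generally predict the next arm, or that enrolment will be biased. The documents do not support either. Only some allocations become certain, nothing suggests that anyone would exploit them, and no bias in any outcome can be quantified from the text. Nor do they support a claim that the completion percentage is directly biased: it is pooled over all randomised patients, so steering patients between arms touches it only indirectly.

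**Conclusion.** The point holds as a modest design weakness. A constant block length, one centre and an unblinded team together allow some allocations to be known in advance: at most 22.0, 14.7, 10.5 or 8.0 of 44 for lengths 2, 4, 6 or 8, and fewer where the length has to be inferred.

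This rests on three assumptions: the unstated length is one of those shown, there is a single unstratified sequence, and those who influence entry see the running list. What is exposed is the share of eligible patients randomised and the balance of the arms in the unadjusted acid-contact-time comparison. The sample size is unaffected. In a feasibility study without hypothesis tests this is worth correcting because the correction is cheap, and it does not put the trial's main purpose in doubt.

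**What to change.** Under Randomisation procedures, replace fixed-block randomisation with permuted blocks of randomly varying size. State that the sizes are chosen by the trials unit and withheld from site staff. Apply this to allocations not yet made, and carry it into the definitive trial.

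**Gain.** With 4/6 or 4/6/8 as illustrative sizes, about 2.5 or 1 of 44 allocations would be certain, against 14.7 for a known fixed length of 4.

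**Cost.** The trials unit has to change how the remaining list is generated; the article does not show how much work that is in its purpose-built system. The final split may depart from 22/22, with a difference between arms of up to half the largest block. With a largest block of 8 that is at most 4, or 24 against 20. This is tolerable where the analysis is descriptive.
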